## Abstract

**Background:**

Anastomotic leakage (AL) remains the most important complication following colorectal surgery, and is associated with high morbidity and mortality rates. Previous research has focused on identifying risk factors and potential biomarkers for AL, but the sensitivity of these tests remains poor.

**Objective:**

This prospective multicenter observational study aims at combining multiple parameters to establish a diagnostic algorithm for colorectal AL.

**Methods:**

This study aims to include 588 patients undergoing surgery for colorectal carcinoma. Patients will be eligible for inclusion when surgery includes the construction of a colorectal anastomosis. Patient characteristics will be collected upon consented inclusion, and buccal swabs, breath, stool, and blood samples will be obtained prior to surgery. These samples will allow for the collection of information regarding patients’ inflammatory status, genetic predisposition, and intestinal microbiota. Additionally, breath and blood samples will be taken postoperatively and patients will be strictly observed during their in-hospital stay, and the period shortly thereafter.

**Results:**

This study has been open for inclusion since August 2015.

**Conclusions:**

An estimated 8-10% of patients will develop AL following surgery, and they will be compared to non-leakage patients. The objectives of this study are twofold. The primary aim is to establish and validate a diagnostic algorithm for the pre-operative prediction of the risk of AL development using a combination of inflammatory, immune-related, and genetic parameters. Previously established risk factors and novel parameters will be incorporated into this algorithm, which will aid in the recognition of patients who are at risk for AL. Based on these results, recommendations can be made regarding the construction of an anastomosis or deviating stoma, and possible preventive strategies. Furthermore, we aim to develop a new algorithm for the post-operative diagnosis of AL at an earlier stage, which will positively reflect on short-term survival rates.

**Trial Registration:**

Clinicaltrials.gov: NCT02347735; https://clinicaltrials.gov/ct2/show/NCT02347735 (archived by WebCite at http://www.webcitation.org/6hm6rxCsA)

## Introduction

Surgery remains the predominant curative treatment for patients with colorectal cancer (CRC), but can lead to severe post-operative complications, of which anastomotic leakage (AL) is the most feared. AL occurs in 8-15% of patients undergoing colorectal surgery and is associated with high morbidity and short-term mortality rates of up to 39% [1-4]. AL often requires one or more re-interventions, leading to a significant increase in length of hospital stay and subsequently to high health care costs [3]. Some authors even suggest that AL is associated with an impaired oncological prognosis [5-8]. Both decreased disease-specific survival (odds ratio [OR] 1.75) [9,10] and an increased local recurrence rate of CRC (OR 2.9) [10] have been reported.

In the past decades, important risk factors for AL such as male gender [4], neo-adjuvant chemotherapy [11], tumor size [12], malnutrition [13], smoking [14], steroid treatment [1,15], and the use of non-steroidal anti-inflammatory drugs (NSAIDs) [16] have been identified. Despite the determination of these risk factors for AL, surgeons’ prediction of the risk to develop AL for the individual patient remains inaccurate [17]. Despite decades of extensive research on preventive methods, the introduction of innovative surgical techniques, and fast-track protocols, incidence rates of AL have remained stable [18].

A recently conducted study in one of the participating centers, that can be considered a pilot study, suggests that pre-operative levels of a certain plasma marker (intestinal fatty acid binding protein, I-FABP) can predict the development of AL in patients undergoing CRC surgery. I-FABP is present in mature enterocytes of the small and large intestine, and is released upon intestinal damage [19]. It is hypothesized that increased plasma levels of I-FABP are the result of an underlying clinical condition of the gastrointestinal tract, predisposing the patient to AL [20].

Cumulative evidence in the literature suggests that perioperative pain treatment with NSAIDs, commonly prescribed analgesics that inhibit cyclo-oxygenase 2 (COX-2) expression, increase the risk of AL [16,21,22]. COX-2 knockout mice have an increased risk of developing AL, and this risk can be reduced by the administration of prostaglandin E2, a product of COX-2 [23]. Another study conducted by our research group has demonstrated that decreased COX-2 expression, due to a polymorphism in the COX-2 gene, leads to an increased risk of the development of AL [23]. Furthermore, it has been shown that patients with different genotypes of mannose-binding lectin (MBL), an important complement factor of the immune system, respond differently to intestinal damage [24].

In the pilot study mentioned previously, it was shown that a combination of C-reactive protein (CRP) and calprotectin levels in plasma provides high diagnostic accuracy for AL during the post-operative period. Finally, we have shown that functional compromise (characterized by malnutrition, frailty, and sarcopenia) is associated with post-operative morbidity and mortality [25]. Malnutrition, as indicated by high Short Nutritional Assessment Questionnaire (SNAQ) scores, and sarcopenia were predictive for, or showed a trend towards, prediction of AL.

Based on previous literature and both our experimental and clinical data, we hypothesize that the occurrence of AL is partly due to patient-derived factors such as a compromised immune response, sarcopenia, genetic predisposition, and an aberrant intestinal microbiome composition, and that the post-operative course can be further influenced by surgical stress, ischemia, and a derailed systemic response. Our hypothesis is that, based on these parameters, individual risks for the development of AL can be assessed pre-operatively.

Besides the obvious improvements that can be made regarding pre-operative risk assessment, the post-operative recognition and management of AL has also proven to be challenging. The timing of AL diagnoses varies greatly, from post-operative day 3 to beyond 30 days, with a mean of 12.7 days post-operatively [26]. Abnormal vital signs and biochemical tests are quite common following the construction of a colorectal anastomosis, and can therefore not be used adequately in the diagnosis of AL. The presentation of AL can vary from abdominal pain and low-grade fever to peritonitis and severe sepsis. This nonspecific course of AL often delays radiologic imaging, and even if this test is undertaken, the diagnoses frequently remain uncertain. Previous research has presented false-negative rates varying from 17-52% for both contrast enemas and computerized tomography (CT) scans [27], resulting in a significant delay of re-intervention [28].

Since a delayed diagnosis of AL is associated with poor outcome [29] and premature re-intervention could lead to a high number of negative re-explorations, one should outweigh the risks of a delayed intervention and the morbidity of re-intervention. Physicians are armed with a restricted number of parameters contributing to risk analysis for the development of AL, with only limited specificity and sensitivity.

### Study Objectives

The objectives of the Predictive Factors of Anastomotic Leakage after Colorectal Surgery (REVEAL) study are twofold. The primary aim of this study is to establish a risk assessment tool for the pre-operative prediction of the development of AL based on a combination of inflammatory, immune-related, and genetic parameters. This algorithm should enable surgeons to make an adequate estimation for every individual patient’s risk of AL, and will eventually aid in the decision-making process regarding the construction of anastomoses and deviating ostomies. In addition, this study aims to provide additional post-operative biomarkers for AL diagnosis at earlier stages, thereby reducing the clinical impact of this feared complication.

## Methods

This is a study protocol for a multicenter, prospective observational study. This study is approved by the Medical Ethical Committee of the Maastricht University Medical Centre. A written informed consent is required from all participating patients and the trial will be conducted in compliance with the rules of *Good Clinical Practice*.

### Study Population

All patients aged >18 years undergoing elective colorectal surgery for colorectal carcinoma, with the construction of an anastomosis, in one of the three participating centers are eligible for inclusion. Patients with large adenomas (large tubular, tubulovillous, or sessile) that cannot be resected radically by means of endoscopy will be included as well, provided that the adenoma is removed surgically with the construction of a colorectal anastomosis. Sample size analysis revealed that 588 consecutive patients have to be included at the outpatient department, prior to surgery. Patients undergoing colorectal surgery for benign conditions, those with permanent stomata without anastomosis, or patients that are unable to give informed consent will be excluded from participation in this study, as well as pregnant patients. If no anastomosis is constructed during surgery, the patient will be withdrawn from the study. Eligibility for inclusion will be determined during a visit at the outpatient department. Upon approval, the patient will receive oral and written information regarding the study, after which he/she will have ample time to reconsider participation. Informed consent will be signed in the presence of the surgeon or researcher.

### Study Outline

Patients will be admitted to the ward one day prior to surgery, and perioperative care will be performed according to *Enhanced Recovery After Surgery* guidelines for elective colonic surgery [30]. Due to the compelling evidence regarding the detrimental effects of NSAIDs on intestinal wound healing, these drugs will not be administered in this patient population during the perioperative phase. Instead, adequate pain treatment will be provided by means of acetaminophen and opioids if necessary. A *Data Safety Monitoring Board* has been commissioned to evaluate the quality of data collection and monitor patient safety. A web-based system was constructed in order to facilitate the collection of standardized and coded patient data.

The primary end point of this study is post-operative AL, occurring during the first 30 days after surgery, either during hospital admission or following discharge. AL is defined as a communication between the intra- and extra-luminal compartments, resulting from a defect in the integrity of the intestinal wall. Leakage from the suture or staple line from a neorectal reservoir, as well as an abscess near the anastomosis, are also considered leaks [31]. The impact of AL on clinical management is recorded, together with the presence of subclinical (radiological) leaks.

Upon hospital admission, a buccal swab will be performed in order to collect DNA to screen for MBL and COX-2 polymorphisms. In addition, composition of volatile organic compounds (VOCs) in exhaled air will be measured both pre- and post-operatively. Various metabolic processes produce markers that are released into the circulation and, upon passage through the pulmonary system, can be identified as volatile products in exhaled air. The occurrence of (chronic) inflammation and/or oxidative stress can result in the excretion of volatile compounds that generate unique VOC patterns [32]. Furthermore, several baseline characteristics will be acquired prior to surgery, and stool will be collected on three occasions (pre-operatively, post-operatively and at the outpatient department during a control visit) in which the intestinal microbiome can be identified. It has been suggested that the microbiota play an important role in the pathogenesis of AL [33] and that the composition of the intestinal flora can be altered by surgical stress [34]. Plasma will be collected prior to surgery and on post-operative days 1, 3, and 5, in order to determine the concentration of markers for enterocyte damage (eg, I-FABP, citrullin, and calprotectin), transmural ischemia (eg, smooth muscle protein 22), and general inflammation markers (eg, CRP and leukocyte count).

In addition, SNAQ and Malnutrition Universal Screening Tool scores are obtained to assess the nutritional status of the patient, and CT-images are analyzed for total skeletal muscle cross-sectional area in order to distinguish sarcopenic patients from those in good nutritional health [25]. Generalized atherosclerosis will be assessed using abdominal CT-scans, as this is a proposed risk factor for AL [35,36]. Finally, a tissue sample will be obtained from the resected specimen, on which conventional and immunohistochemical staining will be performed.

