**Statistical Analyses**

The sample size is calculated with a power analysis and is aimed at our main study outcome, AL. From literature, we know that approximately 10% of all colorectal patients receiving an anastomosis will develop AL [14,37]. The aim of the study is to detect significant and clinically relevant differences between the AL group and the non-AL group. Therefore, we used data from a previous study undertaken by our group to determine sample size [20]. We chose our least significant finding, to avoid the study being underpowered. Based on an effect size of 0.41 (calculated with mean calprotectin levels and SD on day 1), with a power of 0.80 and a 95% confidence interval, the total sample size will be 560, of whom an estimated 51 patients will develop AL. Assuming a 5% dropout rate, the total number of patients that needs to be included in this study is 588.

After data collection, normality will be tested by the D’Agostino-Pearson test. Student’s t-tests will be used for between-group comparisons for continuous data. Dichotomous variables will be compared using Pearson’s chi-squared test. All data will be presented as mean and standard error of the mean. The area under the curve of receiver operating characteristic (ROC) curves will be used to calculate the diagnostic ability of the studied markers predicting AL. The area under the ROC curve is a summary measure of accuracy, lying in the range from 0.5 to 1, with 1 indicating perfect discrimination and 0.5 indicating no discrimination capacity. To determine the most ideal combination of markers, logistic regression analyses will be performed.

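### No analysis step named in the article separates new post-operative information from a difference already present before surgery; this matters chiefly for I-FABP

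*Protocol article*

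**What the plan says.** Study Outline fixes the sampling: "Plasma will be collected prior to surgery and on post-operative days 1, 3, and 5". I-FABP, calprotectin and CRP are among the plasma markers listed, and exhaled volatile compounds are also measured before and after surgery. These markers are therefore repeated measures in the same patient.

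The Study Objectives section sets two aims: pre-operative prediction of leak risk, and further post-operative markers that allow earlier diagnosis.

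The Introduction reports a pilot suggesting that the pre-operative plasma level of one marker ("intestinal fatty acid binding protein, I-FABP) can predict the development of AL in patients undergoing CRC surgery") is informative, and attributes this to an underlying bowel condition that predisposes to leakage. It gives no size for the difference. For the post-operative period the pilot evidence cited is CRP combined with calprotectin.

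Statistical Analyses then states: "Student’s t-tests will be used for between-group comparisons for continuous data". It adds ROC areas for the diagnostic ability of the markers, and logistic regression to find the best marker combination. The sample size rests on a post-operative level: "Based on an effect size of 0.41 (calculated with mean calprotectin levels and SD on day 1").

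**The concern.** For I-FABP the two aims share one measurement scale. If patients who later leak start with higher I-FABP, and a patient's level before surgery is correlated with the level afterwards, the groups will differ on days 1, 3 and 5 even if surgery and the leak add nothing. A two-group t-test or a single-marker ROC area on the post-operative level cannot tell that apart from a signal produced by the leak. The marker could then be credited to the early-diagnosis aim when it only repeats what the risk-prediction aim already knew.

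There is a second, smaller cost. For a marker with no baseline difference, leaving out the pre-operative value keeps predictable between-patient variation in the comparison and gives up power in a study that expects only about 51 leaks.

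**Working it through.** **Inputs from the article (Statistical Analyses).** Effect size 0.41, from day-1 calprotectin; "with a power of 0.80 and a 95% confidence interval", read as two-sided alpha 0.05; and "the total sample size will be 560, of whom an estimated 51 patients will develop AL", so 51 v 560 − 51 = 509.

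**Assumed inputs, not in the article.** Baseline difference *b* between leak and non-leak patients: 0.2, 0.41 or 0.6 SD. Within-group pre/post correlation *r*: 0.3, 0.5 or 0.7. The value 0.41 is borrowed only as a convenient mid-range size. In the article it belongs to another marker, measured after surgery.

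**Step 1: the plan's own figure.** The non-centrality is d × √(n1·n2/(n1+n2)) = 0.41 × √(51 × 509/560) = 0.41 × 6.81 = 2.79. The non-central t distribution then gives power 0.796, which agrees with the stated 0.80. Solving for n at a 1:10 ratio gives 52 leaks and 572 patients, within 3% of 560. The planned size reproduces.

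**Step 2: carry-over with no post-operative effect.** Assume SD 1 at both times, and that the post-operative value depends on group only through the measured pre-operative value. Then:

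- post-operative difference = r × b
- AUC of the post-operative level = Φ(r·b/√2)
- probability that the t-test is significant in the leak direction: non-central t with non-centrality 6.81 × r × b (2.5% if there were no difference at all)

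| b (SD) | r | Post-op difference (SD) | AUC | Significant, leak direction |
|---|---|---|---|---|
| 0.2 | 0.3 | 0.06 | 0.52 | 6% |
| 0.2 | 0.5 | 0.10 | 0.53 | 10% |
| 0.2 | 0.7 | 0.14 | 0.54 | 16% |
| 0.41 | 0.3 | 0.12 | 0.53 | 13% |
| 0.41 | 0.5 | 0.21 | 0.56 | 29% |
| 0.41 | 0.7 | 0.29 | 0.58 | 50% |
| 0.6 | 0.3 | 0.18 | 0.55 | 23% |
| 0.6 | 0.5 | 0.30 | 0.58 | 53% |
| 0.6 | 0.7 | 0.42 | 0.62 | 81% |

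**Step 3: what a joint model would show in the same situation.** With normal values and equal variances, the logistic coefficient of the post-operative value given the pre-operative one is proportional to (post-operative difference − r·b)/(1 − r²) = (r·b − r·b)/(1 − r²) = 0. The expected AUC gain over the pre-operative value is also zero. The joint model therefore separates what the t-test and the single-marker AUC cannot.

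**Step 4: power for a marker with no baseline difference and a true effect of 0.41.** Adjustment multiplies the residual SD by √(1 − r²), so the effective size is 0.41/√(1 − r²):

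- r = 0.3: 0.41/0.954 = 0.43, power 0.83
- r = 0.5: 0.41/0.866 = 0.47, power 0.90
- r = 0.7: 0.41/0.714 = 0.57, power 0.97

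The unadjusted power is 0.80.

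**The case against.** A reader might infer that the plan compares raw day 1, 3 and 5 values and never uses the pre-operative one. The article does not say that. It neither specifies raw levels nor excludes change scores or a baseline covariate. The only direct pointer to levels is the day-1 calprotectin effect size. The article is also condensed, and baseline handling may be set out in a fuller document. The logistic regression for marker combinations could hold pre- and post-operative values together. All of this stands, and it limits the point to the steps the article names. As described, though, that regression serves to find the best combination, not to show what a post-operative value adds.

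A reader might also infer that raw-level ROC areas are wrong. They are not. The AUC of a day-3 level correctly describes how well that level separates leaks from non-leaks, whatever the source of the separation. The problem arises only when that AUC is read as new post-operative information.

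Nor can the concern be extended to every marker. A pre-operative difference is suggested for I-FABP only, without a size. None is reported for CRP or calprotectin, which carry the post-operative pilot evidence.

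Finally, much of the table is unimpressive. An AUC of 0.52 to 0.54 would hardly be promoted as a diagnostic test, and at r = 0.3 adjustment gains only three points of power. That is fair, and it is why the priority is not high.

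**Conclusion.** The point holds in a limited form. The steps named in Statistical Analyses do not distinguish a carried-over baseline difference from new post-operative information, although the samples needed to do so are already scheduled. For I-FABP, where the article itself suggests a pre-operative difference, a significant t-test and an AUC above 0.5 after surgery would not by themselves support the early-diagnosis aim.

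The size cannot be fixed from the article. Over the assumed ranges (*b* 0.2 to 0.6 SD, *r* 0.3 to 0.7, no post-operative effect, 51 v 509 patients) the AUC runs from 0.52 to 0.62 and the chance of a significant result in the leak direction from 6% to 81%, that is, from negligible to misleading. These figures also rest on normal values with equal variances, and on carry-over acting through the measured pre-operative value.

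It would go too far to say that the study will report a false diagnostic signal, or that its early-diagnosis aim cannot be met. The article supports neither. The sample size of 560 (588 with dropout) is not affected. Priority: minor to moderate.

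**What to change.** For each marker measured before and after surgery, chiefly I-FABP, add a single-marker logistic model for leakage that contains the patient's pre-operative and post-operative values together. Report the adjusted odds ratio of the post-operative value and the AUC gain over the pre-operative value alone, and base any claim of added post-operative information on these. Keep the raw-level AUCs and label them as the discrimination of the measured level.

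The cost is a few sentences of analysis text and one extra term per single-marker model, with no new samples or patients. There is one limit: with about 51 events, baseline terms for all markers should not be forced into one joint model. The added-value question should be settled marker by marker before the combination is built.

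### The one stated use of CT skeletal muscle area, a continuous measurement, is a sarcopenic/well-nourished split, which discards information about a candidate predictor in a study expecting about 51 leaks

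*Protocol article*

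**What the plan says.** Study Outline gives one purpose for the CT muscle measurement: "CT-images are analyzed for total skeletal muscle cross-sectional area in order to distinguish sarcopenic patients from those in good nutritional health". The Introduction also works with the label rather than the area. It lists sarcopenia among the patient factors in the hypothesis and reports that in the group's previous work high malnutrition scores and "sarcopenia were predictive for, or showed a trend towards, prediction of AL".

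Statistical Analyses sets general rules by type of variable: "Student’s t-tests will be used for between-group comparisons for continuous data", and "Dichotomous variables will be compared using Pearson’s chi-squared test". ROC areas are to describe how well the studied markers predict leakage, and logistic regression is to find the best combination. The section does not assign muscle area or sarcopenia to any of these analyses. The article gives no cut-off, no sarcopenia prevalence and no effect size for muscle area.

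**The concern.** A cut treats two patients just either side of it as wholly different, and all patients on the same side as identical. That fits poorly with the primary aim in Study Objectives, a tool that estimates each individual patient's risk. Only about 51 leaks are expected, so information per predictor is scarce, and the previous evidence on sarcopenia is described as somewhere between predictive and a trend. With a signal of that strength, lost information can decide whether a predictor is kept. If the label alone were used, its AUC would also come from a single point on the ROC curve and would be read beside AUCs of plasma concentrations, for which the article states no cut.

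**Working it through.** **Inputs from Statistical Analyses**
- Effect size: "Based on an effect size of 0.41 (calculated with mean calprotectin levels and SD on day 1"). It belongs to a plasma marker, not to muscle area.
- Error rates: "with a power of 0.80 and a 95% confidence interval", read as two-sided 5%.
- Numbers: "the total sample size will be 560, of whom an estimated 51 patients will develop AL", so 560 − 51 = 509 without leakage. 51/560 = 9.1%, in line with "approximately 10% of all colorectal patients receiving an anastomosis will develop AL".

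**Assumptions not in the article.** Muscle area is normal with equal SD in both groups and shifted by d SD in leak patients. Overall sarcopenia prevalence is 10% to 70%. For the illustration, d = 0.41 is borrowed.

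**Step 1: the plan's own figure.** With one leak per ten non-leaks, the number of leaks needed is (1 + 1/10) × ((1.96 + 0.842)/0.41)² = 51.4, and 51 × 11 = 561. Adding 5% gives 560 × 1.05 = 588. The stated 560 and 588 are reproduced.

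**Step 2: continuous analysis.** The non-centrality is 0.41/√(1/51 + 1/509) = 2.79. The non-central t distribution gives power of 79.6%. AUC = Φ(0.41/√2) = 0.614.

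**Step 3: split analysis.** Choose the cut c so that (51·Φ(c + d) + 509·Φ(c))/560 equals the assumed prevalence. Then p1 = Φ(c + d) is the proportion sarcopenic in leak patients and p2 = Φ(c) that in the others. Power = Φ((p1 − p2 − 1.96·s0)/s1), with s0 the pooled and s1 the unpooled standard error. AUC = 0.5 + (p1 − p2)/2.

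Example at 30%: p1 = 0.4385, p2 = 0.2861, s0 = 0.0673, s1 = 0.0723. Power = Φ((0.1524 − 0.1319)/0.0723) = Φ(0.28) = 61.1%. AUC = 0.5 + 0.1524/2 = 0.576.

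| Sarcopenia prevalence | Power, split | Loss from 79.6% (points) | AUC, split |
|---|---|---|---|
| 10% | 50.6% | 29.0 | 0.544 |
| 20% | 58.3% | 21.2 | 0.565 |
| 30% | 61.1% | 18.4 | 0.576 |
| 40% | 61.2% | 18.4 | 0.581 |
| 50% | 59.1% | 20.5 | 0.580 |
| 60% | 54.7% | 24.9 | 0.574 |
| 70% | 47.2% | 32.3 | 0.564 |

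The smallest loss is 18.1 points, at 35% (power 61.5%). Simulated chi-squared tests (100,000 per prevalence) agree with the formula to within 1.5 points over this range.

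**Step 4: other effect sizes, prevalence 10% to 70%**

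| d | Power, continuous | Loss of power (points) | AUC, continuous | AUC, split |
|---|---|---|---|---|
| 0.2 | 27.5% | 8 to 13 | 0.556 | 0.519–0.540 |
| 0.3 | 53.2% | 15 to 25 | 0.584 | 0.530–0.559 |
| 0.41 | 79.6% | 18 to 32 | 0.614 | 0.544–0.581 |
| 0.5 | 92.5% | 14 to 29 | 0.638 | 0.555–0.599 |
| 0.6 | 98.3% | 7 to 19 | 0.664 | 0.569–0.618 |
| 0.8 | over 99.9% | 1 to 4 | 0.714 | 0.598–0.655 |

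The power loss is small only where the effect is large enough to be found either way. The AUC falls in every case.

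**The case against.** The strongest reply is that Study Outline describes data collection, while Statistical Analyses never names sarcopenia. The t-test rule covers a measured area as readily as the chi-squared rule covers a label. Nothing says that the area is discarded, or how it is coded in the logistic model, and a condensed article may leave coding to the full plan. This stands against the stronger reading that a reader might infer, namely that the protocol prescribes chi-squared for sarcopenia and excludes the area from the ROC and logistic analyses. It does not remove the point: the two-group split is a stated purpose, not a gap, and nothing in the article points to continuous use.

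The second reply is that the figures are not properties of muscle area. The 0.41 is calprotectin's, the prevalence is assumed, and a normal shift builds in a loss that a true threshold effect might not show. If the sarcopenia definition already allows for sex or height, the label is also not a simple cut of the modelled variable. All of this stands, so the figures are an illustration. The article claims no threshold effect, however.

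The third reply is that the consequences are limited. The primary aim is worded in terms of inflammatory, immune-related and genetic parameters, and sarcopenia is one hypothesised factor among several. That is also correct, and it keeps the point to one predictor.

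**Conclusion.** The point holds in a limited form. The only stated use of a continuous CT measurement is a two-group split, and under a normal-shift model with 51 and 509 patients that split loses power and AUC at every cut examined. With the borrowed effect size of 0.41 and 10% to 70% sarcopenia, the power loss is 18 to 32 points. Over effect sizes of 0.2 to 0.8 it is about 1 to 32 points.

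A reader might take 18 to 32 points as the known cost for this predictor. The article does not support that, because it gives neither an effect size nor a prevalence for muscle area. Nor does the point imply that the study is underpowered: the sample size was set on calprotectin and is unaffected.

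**What to change.** State in Statistical Analyses that CT skeletal muscle area enters the between-group comparison, the ROC analysis and the logistic regression as a continuous predictor. Take sex into account, since the Introduction lists male sex as a risk factor and muscle area can be expected to differ by sex. Keep the sarcopenic/non-sarcopenic split as a descriptive or secondary presentation.

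Indexing to height, if height is collected, and a simple non-linear term are optional. With about 51 events, each added parameter has a cost.

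The change is to analysis wording only: the area is already read from the CT images, and no further patients are needed. The small downside is that a continuous value is less easy to present than a yes/no label.
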